**IV. STUDY DESIGN.**

- a. **Trial Design:** A multi-institution, randomized, single-blind clinical trial
  - b. **Participants and Exclusion Criteria:** Eligible subjects identified from the medical record will be those who are 1) scheduled to undergo RALP surgery, 2) willing to consent to the surgery being performed by one of the surgeons participating in the study, and 3) willing to be assigned by randomization to one of the two groups in the study. Exclusion criteria are 1) prior prostate surgery, ablation, radiation, or androgen deprivation therapy, 2) lack of 3 Tesla or 1.5 Tesla with endorectal coil preoperative MRI imaging, and 3) inability to give informed consent.
  - c. **Randomization:** Each case will be assigned to one of the two preparation methods by a randomization procedure that is stratified by surgeon. Each surgeon-specific randomization schedule will be prepared using permuted blocks of size 2; i.e., each 2-patient block will be some permutation of {VR-aided, Control}. Thus, each surgeon's cases will be randomized in a 1:1 ratio. Use of permuted blocks thus avoids any confounding of preparation method with temporal trends (e.g., trend due to a learning curve.)
- Sequentially numbered opaque sealed envelopes (SNOSEs) will be prepared for each individual surgeon. Each envelope will contain the treatment assignment for one case (intervention or control). There will be an equal number of envelopes containing intervention assignments and control assignments; the total number of envelopes provided to each surgeon will be determined based on the surgeon's historical/anticipated case volume. The treatment code will remain concealed inside the envelope until the moment the case is ready to be prepared.

- d. **Blinding:** Patients, personnel gathering data from the video review, and statistician will be blinded. Control and intervention groups identifiers will be known only to the research personnel opening the sealed envelope for random group assignment and extracting patient data from the electronic medical record.
- e. **Intervention:** For intervention cases, surgeons will be provided with a 3D model to view (a) prior to the operation in addition to the MRI and biopsy results and (b) during the operation in addition to the MRI. For control cases, surgeons will view only the MRI and biopsy results prior to the operation and during the operation itself.

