- f. **3D Model Creation and Delivery:** MRI scans will be deidentified and sent in Digital Imaging and Communications in Medicine (DICOM) format to Ceevra, Inc., where a patient-specific 3D model for each intervention patient will be created. The Prostate Imaging-Reporting and Data System (PIRADS) score will be used to identify and label prostate lesions. In addition, the biopsy report, will be used to create a patient-specific pathology map that will be included in the model to assist the surgeon in understanding the location of biopsy-proven cancer within the prostate. Models will be delivered to a mobile application on the surgeon's smartphone (Ceevra Reveal) and viewed as described above. In addition, the surgeon may view the model picture-in-picture on the robotic console screen using a video cable connection between the surgeon's smartphone and the surgical robot.
- g. **Outcomes Measures and Covariates:** The primary outcome measure is oncologic outcomes after RALP. This outcome will be measured at three time points: immediately postoperative, short term, and a final assessment when oncologic and functional outcomes have reached a steady state. Oncologic outcomes will be measured as margin status (positive or negative), PSA (linear and detectable/undetectable) at the initial assessment (which in most cases is three months postoperatively but may occur any time between 3 and 6 months), and PSA ( $>0.1$ ) at the final assessment (to be collected after 18 months but no later than 24 months). Additionally, any use of androgen deprivation therapy or radiation therapy will be captured at 24 months as an adverse oncologic outcome.
- Secondary outcomes are the urinary and sexual function of the patient, measured at the same three time points as above. For urinary function, this is bladder neck sparing (yes or no), measured immediately postoperatively, and incontinence pads per day, measured at both 3-6 months and 18-24 months postoperatively. For sexual function, this is nerve sparing (none, left, right, or bilateral), measured immediately postoperatively, followed by SHIM score, measured at both 3-6 months and 18-24 months postoperatively.
- Demographic data, disease-specific, surgery-specific, and surgeon-specific covariates will be collected from the medical record as well, see Appendix A.

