- h. **Sample Size:** Sample size was calculated using prior data, including previous trials using 3D models in robotic partial nephrectomy. Previously we noted an effect size of 0.44 regarding the difference of outcome measures between 3D

model-aided and control groups. To account for multiple endpoints, we raised the sample size by 15%. Using the above method and paired t-test, the sample size of 90 (45 per arm) provided 80% power to detect clinically significant differences in our primary outcome measures with  $\alpha=0.05$ .

- i. **Statistical analysis:** Initial analysis will compare baseline characteristics between cases performed with (intervention) or without (control) models involved in preoperative planning. A two-sample t-test will be employed to compare means between groups and Chi-Square test or Fisher's exact test to assess the association between categorical variables. For outcome measures, the appropriate test will be used as described above to compare groups. To mitigate type I error due to multiple comparisons, and if the randomization yields balanced cohorts, a Bonferroni correction may be utilized for the primary and secondary outcomes. If randomization yields groups with statistically or clinically significant differences, adjusted differences between groups will be studied using a linear mixed model to regress the endpoint variables on covariates listed above, or the logistic mixed model, as appropriate.

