## Appendix A

### Study Covariates

#### 1. Patient parameters

- a. Age
- b. Race
- c. Surgeon ID and tier
- d. MRI Fusion Biopsy used
- e. Preop and postop Gleason score
- f. Preop PSA
- g. Preop SHIM score
- h. Preop use of erectile aid
- i. Prostate volume
- j. Number of masses
- k. Mass size
- l. Extracapsular extension
- m. Tumor location
- n. Tumor orientation
- o. PIRADS score
- p. Perineural invasion
- q. SV invasion
- r. Risk category
- s. Clinical stage
- t. Oncologic stage
- u. Number of positive biopsy cores
- v. Use of erectile aids (pre and postoperatively)

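### The default outcome tests ignore the surgeon strata and preoperative SHIM, and adjustment waits on chance baseline imbalance, which costs some power for SHIM and leaves the choice of analysis open

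*Combined protocol and SAP*

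**What the plan says.** - **Allocation.** Section IV.c assigns each case "by a randomization procedure that is stratified by surgeon", in blocks of two, so the arms are balanced 1:1 within surgeon.
- **Default analysis.** Section IV.i states: "A two-sample t-test will be employed to compare means between groups". It names chi-square or Fisher's exact test for categorical variables and carries the same tests over to the outcomes. None of them has a surgeon term or a baseline value.
- **Conditional analysis.** Section IV.i continues: "If randomization yields groups with statistically or clinically significant differences, adjusted differences between groups will be studied", by a linear or logistic mixed model on the listed covariates. It gives no threshold for clinical significance and no rule for which covariates enter. The optional Bonferroni correction also depends on observed balance.
- **SHIM.** Section IV.g makes it a secondary outcome: nerve sparing is "followed by SHIM score, measured at both 3-6 months and 18-24 months postoperatively". Appendix A lists "Preop SHIM score" and surgeon ID among the covariates, so both are collected but used only on the conditional branch.

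**The concern.** An analysis should reflect the way patients were randomised. When strata are balanced by design and then ignored, between-surgeon variation stays in the error term, so the standard error is too large and the test is conservative. Preoperative SHIM can be expected to predict postoperative SHIM, and leaving it out discards precision already paid for.

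The trigger makes this worse. In a properly randomised trial a significant baseline difference is a chance finding and says little about which covariates matter for the outcome. Surgeon is balanced by design, so it will rarely be the variable that sets the trigger off; the stratification factor enters the model only when something else happens to differ. Because clinical significance is undefined, the switch also rests on a judgement made during analysis. At stake are a single prespecified answer for each outcome and some power in a 90-patient trial.

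**Working it through.** **Inputs from the documents (section IV.h):** two arms of 45, effect size 0.44, alpha 0.05 (taken as two-sided).

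**Assumed, because the documents give no figures:** surgeon ICC 0.1 to 0.2; correlation r of preoperative with postoperative SHIM 0.4 to 0.6; 9 surgeons with 10 patients each; about 20 independent baseline tests; 0.44 applied to SHIM.

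**1. The plan's own figure.** The plan says "the sample size of 90 (45 per arm) provided 80% power", from a paired t-test with a 15% increase.
- Paired: ((1.960 + 0.842)/0.44)² = 40.5 pairs; × 1.15 = 46.6, so 47 per arm or 94 in total. The stated 90 is not reproduced. Power at 45 pairs is Φ(0.44√45 − 1.960) = 84%.
- Two-sample, the test section IV.i names: 2 × 40.5 = 81.1, so 82 per arm. Power at 45 per arm is Φ(0.44√22.5 − 1.960) = Φ(0.127) = 55%.

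This mismatch is a separate matter. The 55% is used below only as a starting point.

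**2. How often the trigger fires by chance.** 1 − 0.95²⁰ = 64%; 1 − 0.95¹⁰ = 40%. With 20 tests and pairwise correlation 0.2, simulation gives 59%. Appendix A lists 22 patient items, but some are postoperative, one is repeated and surgeon is balanced, so 20 is a rough count.

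**3. Type I error of the default test.** Ignoring strata overstates the SE by 1/√(1 − ICC). The true level is 2(1 − Φ(1.96/√(1 − ICC))) = 3.9% at ICC 0.1 and 2.8% at 0.2.

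**4. Power for SHIM at ICC 0.1 (normal approximation).**
- Never adjust: Φ((2.087 − 1.960)/√0.9) = 55.3%.
- Always adjust: Φ(0.44√(22.5/(0.9(1 − r²))) − 1.960).
- Plan as written, treating the trigger as unrelated to the outcome: 0.642 × always + 0.358 × never.

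| r | Never adjust | Plan as written | Always adjust | Loss (points) |
|---|---|---|---|---|
| 0.4 | 55.3% | 62.8% | 67.0% | 4.2 |
| 0.5 | 55.3% | 66.0% | 71.9% | 5.9 |
| 0.6 | 55.3% | 70.2% | 78.5% | 8.3 |

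Simulations of the conditional rule, with surgeon and preoperative SHIM as the adjusted model, agree: about 60-71% as written against 65-80% always adjusted, a loss of about 4 to 9 points. If only 10 variables were tested, the trigger would fire less often and the loss would grow: 0.599 × (67.0 − 55.3) = 7.0 points at r = 0.4, and 0.599 × (78.5 − 55.3) = 13.9 at r = 0.6.

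**5. Type I error of the conditional rule.** Simulated at 4.0-5.0% when followed. If the better of the two analyses were chosen, it is 6.0-7.4% (r 0.3 to 0.7).

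**6. Primary measures.** For a binary measure at an assumed 30% against 12%, simulated with 9 surgeons:

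| Surgeon log-odds SD | Chi-square | Surgeon-stratified CMH |
|---|---|---|
| 0 | 58.2% | 56.4% |
| 0.5 | 56.9% | 56.5% |
| 1.0 | 51.3% | 55.0% |

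For continuous PSA at the first assessment, adding surgeon alone at effect 0.44 gives 59.5% (ICC 0.1) or 64.6% (ICC 0.2), against 55.3% or 55.7% unadjusted. The plan's loss is then 0.358 × 4.2 = 1.5 points, or 0.358 × 8.9 = 3.2 points.

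**The case against.** The best defence is that the plan errs on the safe side. The default test is conservative, the conditional rule does not raise type I error, and the trigger looks at baseline data in what section IV.i calls the initial analysis, with a statistician who is blinded under section IV.d. All of that stands. A reader might infer that the conditional switch inflates false positives; it does so only if someone departs from the rule and picks the better result. Blinding limits steering towards one arm, but it does not supply the missing threshold or covariate list.

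A second defence is that comparing never adjusting with always adjusting exaggerates the harm. That is right: at r = 0.6 the contrast is 55% against 79%, but the plan adjusts in about 64% of trials under 20 tests, so its own loss there is about 8 points. A reader might also charge the low 55% to this issue. It comes mainly from sizing with a paired test and analysing with a two-sample one, and it should not be counted here.

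Third, the larger gain concerns a secondary outcome, and the inputs are assumed. The effect size is described only in general terms ("Previously we noted an effect size of 0.44 regarding the difference of outcome measures"), not for SHIM. This limits the size of the point but not its direction. The paired t-test does not rescue the plan, because it appears only in the sizing and section IV.i plans no within-surgeon test.

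**Conclusion.** The point holds at moderate size and should be fixed. The text plainly leaves surgeon and preoperative SHIM out of the default tests and lets chance imbalance, or an undefined clinical judgement, decide whether they enter. With about 20 independent baseline tests the switch occurs in about 64% of properly randomised trials.

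The cost is a mildly conservative default test and roughly 4 to 9 points of power on SHIM, given ICC 0.1, r of 0.4 to 0.6, effect 0.44 and 9 surgeons. The loss is larger if fewer baseline variables are tested. For the binary primary measures, stratifying changes power by about -2 to +4 points. The documents therefore do not support a claim that the primary oncologic comparison is seriously weakened, or that its type I error is inflated when the rule is followed. What applies to every outcome, including the primary, is that no single analysis is fixed in advance.

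**What to change.** - Delete the imbalance trigger and prespecify one model per outcome.
- Always include surgeon: as a fixed or random effect for continuous outcomes, and through a surgeon-stratified Mantel-Haenszel test or a logistic mixed model for binary ones.
- For SHIM at both follow-up times, always include preoperative SHIM.
- If other covariates are wanted, name them in advance and restrict them to baseline variables, since Appendix A mixes in postoperative items.
- Keep the baseline table descriptive, with no p-values that decide anything, and report the unadjusted tests as a sensitivity analysis.

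The cost is SAP wording and minor programming; the variables are already collected. For binary outcomes with little variation between surgeons, stratifying may lose up to about 2 points of power.

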#### 2. Surgical technique

- a. Node dissection template, if performed
- b. Assistant port used
- c. SV dissection approach

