#### 3. Operative Parameters

- a. Total operative time
- b. Blood Loss (cc)
- c. Conversion to open (y/n)
- d. Operative complication (y/n)
- a. Hospital stay (days)
- b. Mortality (y/n)
- c. Readmission (y/n)

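### The conditional adjusted model in IV.i is not limited to pre-randomisation covariates, and the only covariate list includes operative and postoperative items that the intervention can affect

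*Combined protocol and SAP*

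**What the plan says.** Section IV.i first compares baseline characteristics, then compares outcomes with unadjusted tests. If randomisation leaves the groups different, statistically or clinically, it moves to a "linear mixed model to regress the endpoint variables on covariates listed above", or a logistic mixed model for binary endpoints.

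The text above IV.i contains no list. Section IV.g names demographic, disease-specific, surgery-specific and surgeon-specific covariates and refers to Appendix A, headed as the study covariates. That is the only covariate list in the document. It mixes three kinds of item:

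- Clearly preoperative values, such as age, preoperative PSA, preoperative SHIM and "Preop use of erectile aid" (part 1, item h).
- Items that combine preoperative and postoperative values: "Preop and postop Gleason score" (item e) and "Use of erectile aids (pre and postoperatively") (item v).
- Items recorded only at or after surgery: all of part 2, for example "SV dissection approach", and all of part 3, for example "Total operative time" and "Operative complication (y/n").

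On timing, section IV.c says: "The treatment code will remain concealed inside the envelope until the moment the case is ready to be prepared". Under IV.e the surgeon then has the 3D model both before and during the operation.

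**The concern.** A randomised comparison stays unbiased under adjustment for variables fixed before allocation. That protection is lost for a variable the allocation can change. If the variable lies on the path from arm to outcome, adjusting for it removes part of the real effect. If it shares an unmeasured cause with the outcome, such as case difficulty, adjusting for it can create an effect where none exists.

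Item v is the clearest case. Preoperative aid use is already item h, so all that item v adds is postoperative use, which is plausibly a consequence of the function that SHIM measures. Operative time, blood loss and complications raise the same problem for margin status, PSA and pads, so the primary outcome is within reach. Read literally, the rule allows an adjusted estimate that no longer answers the randomised question.

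**Working it through.** The plan gives no figure on this point to reproduce. The check is a count of the list, followed by illustrations of size.

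**Count of Appendix A.** Part 1 has 22 entries (a to v), part 2 has 3 and part 3 has 7: 22 + 3 + 7 = 32. Post-randomisation content appears in items e and v (2), all of part 2 (3) and all of part 3 (7): 2 + 3 + 7 = 12. Four more entries do not say whether the value is preoperative or pathological: extracapsular extension (l), perineural invasion (p), seminal vesicle invasion (q) and oncologic stage (t).

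The 12 do not carry equal risk. Postoperative Gleason mainly reflects the tumour and is the least likely to be changed by arm. Aid use and the operative items are the stronger examples.

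**Inputs for size.** From IV.h: 45 per arm, and an effect size of 0.44, treated here as standardised and borrowed only as a reference. Everything else is assumed, because the documents give no path strengths.

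- SE of a standardised mean difference: √(2/45) = 0.211.
- SE of a log odds ratio at an assumed 20% positive-margin rate (9 events and 36 non-events per arm): √(2 × (1/9 + 1/36)) = 0.527.

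**Illustration 1: SHIM adjusted for postoperative aid use.** Function is normal with SD 1 and a true arm difference of 0.44. SHIM equals function, and logit P(aid) = −b × function. In a linear model, the adjusted difference equals 0.44 minus (within-arm SHIM gap between aid users and non-users) × (difference in aid use between arms). Large simulations give:

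| b | Aid use, control vs 3D model | Within-arm gap (SD) | Shift | Adjusted difference | Shift / 0.211 |
|---|---|---|---|---|---|
| 0.5 | 50.1% vs 44.8% | 0.47 | 0.47 × 0.053 = 0.025 | 0.415 | 0.12 |
| 1 | 50.1% vs 41.0% | 0.83 | 0.83 × 0.091 = 0.076 | 0.364 | 0.36 |
| 2 | 50.0% vs 37.0% | 1.22 | 1.22 × 0.130 = 0.159 | 0.281 | 0.75 |

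With no arm effect on function, and none on aid use by another route, the shift is zero.

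**Illustration 2: margin status adjusted for operative time, no true arm effect on margins.** Difficulty U is standard normal. Operative time = a × arm + r × U + √(1 − r²) × noise. Logit P(positive margin) = c + k × U, with c set to give 20%. Adjusted minus unadjusted log odds ratio:

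| k | a | r = 0.3 | r = 0.5 | r = 0.7 |
|---|---|---|---|---|
| 0.5 | 0.2 | −0.03 | −0.05 | −0.07 |
| 0.5 | 0.44 | −0.06 | −0.11 | −0.15 |
| 1 | 0.2 | −0.05 | −0.09 | −0.13 |
| 1 | 0.44 | −0.12 | −0.20 | −0.28 |

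The odds ratio therefore moves from 1.00 to between exp(−0.03) = 0.97 and exp(−0.28) = 0.76. In standard errors, that is 0.03/0.527 = 0.06 to 0.28/0.527 = 0.53. At the upper end a nominal 5% test rejects with probability P(|Z + 0.53| > 1.96), about 8%, holding the SE at its unadjusted value. If the 3D model shortens operative time, the direction reverses.

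**Cross-check with a continuous outcome.** For a mediator, the adjusted effect is 0.44 − (arm-to-mediator) × (mediator-to-outcome):

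- 0.44 − 0.2 × 0.3 = 0.38
- 0.44 − 0.2 × 0.5 = 0.34
- 0.44 − 0.44 × 0.3 = 0.31
- 0.44 − 0.44 × 0.5 = 0.22

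If the true effect is zero, the arm shifts the adjusting variable by 0.44, and that variable shares an unmeasured cause with the outcome (0.5 and 0.5), the spurious effect is −0.44 × 0.5 × 0.5 = −0.11. If arm does not affect the variable, there is no bias. A simulation of 90 patients agrees with these values.

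**The case against.** The best case for the plan is that the context implies baseline adjustment. IV.i opens with baseline characteristics, and its trigger is imbalance produced by randomisation, which can only concern variables fixed beforehand. The link to Appendix A is indirect: the appendix follows IV.i, and with entries such as mortality and readmission it works partly as a data-collection list. Nor could all 32 entries enter a model for 90 patients. At a 20% margin rate there would be only 0.20 × 90 = 18 events, so some selection is unavoidable. Harm therefore needs both a triggered adjustment and the choice of an affected item. The larger shifts also need the strongest assumptions, and for margins all of them together.

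Much of this stands. The baseline-only reading is reasonable, the harm is conditional, and the illustrations rest on assumed inputs. Some of the 12 entries, such as assistant port use, may be surgeon routine that the model never alters.

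It does not settle the matter. IV.i speaks of baseline characteristics for the first comparison and then changes to listed covariates for the model, while IV.g expressly includes surgery-specific ones. No sentence supplies the restriction, and the need to select without a rule leaves the choice open after results are seen.

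Nor is the trigger remote. If the baseline tests were independent at 0.05, the chance of at least one significant difference by luck would be 1 − 0.95¹⁰ = 40% for 10 characteristics, 1 − 0.95¹⁵ = 54% for 15 and 1 − 0.95²⁰ = 64% for 20. Correlation between items would lower these figures, and the clinical-difference route can only add to them.

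**Conclusion.** The concern holds, as something that should be changed. As written, the adjusted analysis may condition on consequences of the intervention, and its estimate can then be biased for the effect of randomised arm. Size and direction cannot be determined from the documents. Under the assumed inputs, the shift is 0.12 to 0.75 standard errors for SHIM and 0.06 to 0.53 for positive margins. That is modest beside sampling error at 45 per arm, but it is systematic and avoidable. There is no bias if no affected item enters the model, and the default unadjusted comparison is untouched. Confidence is medium, because the harm depends on the trigger and on the analyst's choice of covariates.

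**What to change.** 1. Add to IV.i: *Adjusted models will include surgeon, the stratification factor, and otherwise only covariates whose values are fixed before the randomisation envelope is opened; for SHIM these include preoperative SHIM and preoperative aid use (items g and h). No variable recorded during or after surgery will be used for adjustment.* Age and the other baseline items stay eligible.
2. In Appendix A, take the postoperative part out of items e and v. Move it, with parts 2 and 3, under a heading such as *Operative and postoperative data (collected, not used for adjustment)*.
3. For items l, p, q and t, state that only the MRI or biopsy value may serve as a covariate.
4. Optionally, and descriptively only, tabulate postoperative aid use by arm at the 3-6 and 18-24 month SHIM assessments.

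The first three changes need no extra patients, visits or data. The price is some precision lost by not using strongly prognostic postoperative items such as postoperative Gleason. The optional table may need one dated field at each SHIM assessment.

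### The covariate set for the adjusted analysis is not limited to pre-randomisation variables: the only list it can point to includes operative and postoperative items that the 3D model may itself affect

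*Combined protocol and SAP*

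**What the plan says.** Section IV.i compares the arms first with simple tests. Adjustment is conditional: "If randomization yields groups with statistically or clinically significant differences", adjusted differences come from a linear mixed model, or a logistic one where suitable, used to "regress the endpoint variables on covariates listed above". No covariates are listed in IV.i, and no subset, selection rule, baseline restriction or limit on model size is given.

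The nearest earlier mention is IV.g, whose heading includes covariates. It says that demographic, disease-specific, surgery-specific and "surgeon-specific covariates will be collected from the medical record as well, see Appendix A". Appendix A is titled as the study's covariates and has three parts:

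- **Section 1, patient parameters:** 22 lines, including "Preop and postop Gleason score" and a line on erectile-aid use both before and after surgery.
- **Section 2, surgical technique:** 3 lines, including "SV dissection approach".
- **Section 3, operative parameters:** 7 lines, including "Total operative time", blood loss, complications, hospital stay, mortality and readmission.

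Under IV.c the assignment stays concealed until the case is about to be prepared. Under IV.e the surgeon then views the 3D model before and during the operation.

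**The concern.** Adjustment for chance imbalance is legitimate when the covariates are fixed before assignment. A variable that the assignment can change is different. Conditioning on it removes whatever part of the effect passes through it, and can add bias where that variable and the outcome share other causes. The result is no longer the effect of being assigned to the 3D model, which is what the study objective asks about.

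The plan's own rationale makes this more than theoretical. The model is meant to inform how the surgeon plans and operates, and section V surveys whether the operative plan changed. Operative time, blood loss and complications may therefore respond to the intervention. Postoperative erectile-aid use lies close to the SHIM outcome itself. Hospital stay and readmission come after margin status is fixed and cannot explain a baseline difference in it.

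The second issue is size. Most of the primary oncologic measures in IV.g are binary (margin status, detectable PSA, PSA above 0.1, later androgen deprivation or radiation). A long covariate list in 90 patients can leave a logistic model without finite estimates.

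**Working it through.** The plan gives no figure for the adjusted model, so there is none to reproduce. The total of 90 (45 per arm) from IV.h is taken as given. Event rates, mediated shares and the form of the simulated covariates are assumptions.

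**1. Count of Appendix A.** 22 + 3 + 7 = 32 lines.

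| Part | Lines | Timing relative to assignment |
|---|---|---|
| Section 2 | 3 | after |
| Section 3 | 7 | after |
| Section 1, Gleason and erectile aids | 2 | part before, part after |
| Section 1, extracapsular extension, perineural invasion, SV invasion, oncologic stage | 4 | source (imaging, biopsy or specimen) not stated |
| Section 1, remainder | 16 | before |

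So 3 + 7 = 10 lines are wholly post-assignment, 2 are partly so and 4 are unclear. Preoperative erectile-aid use appears twice (1h and 1v), so there are slightly fewer than 32 distinct variables.

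**2. Bias from adjusting for a consequence of treatment.** In a linear model with total effect 0.44 SD (the effect size in IV.h) and a share *s* running through the adjusted variable, the adjusted coefficient is (1 − *s*) × 0.44:

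- *s* = 0.25: 0.75 × 0.44 = 0.33
- *s* = 0.50: 0.50 × 0.44 = 0.22
- *s* = 0.75: 0.25 × 0.44 = 0.11

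Simulation with 45 per arm (4,000 data sets per share) gave 0.329, 0.219 and 0.108. The unadjusted estimates stayed at 0.44.

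**3. Binary endpoints if the full list were entered.** Events per parameter = 90 × rate / (32 + 1), counting one parameter per line plus treatment. Separation was checked by linear programming on simulated sets with independent predictors. The last column gives the rounded range over repeated runs.

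| Assumed event rate | Events | Events per parameter | Sets with separation |
|---|---|---|---|
| 10% | 9 | 9/33 = 0.27 | 97–99% |
| 20% | 18 | 18/33 = 0.55 | about 50% |
| 30% | 27 | 27/33 = 0.82 | 10–15% |
| 40% | 36 | 36/33 = 1.09 | 2–3% |

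Multi-level items (race, stage, location) use more than one parameter each. At 40 covariate parameters the ratios fall to 0.22, 0.44, 0.66 and 0.88.

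**4. Continuous endpoints if the full list were entered.** Residual degrees of freedom are 90 − 32 − 2 = 56, so the model can be fitted. With covariates unrelated to outcome, simulation (1,000 sets) raised the standard error of the treatment effect from 0.213 to 0.257 SD, a ratio of 1.21. The theoretical ratio for random covariates is √[(90 − 3)/(90 − 3 − 32)] = √(87/55) = 1.26. The loss of precision is therefore 20 to 26%. Prognostic covariates would offset some of it.

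**5. A short baseline set for comparison.** With 3 single-parameter covariates plus treatment, events per parameter are 2.25, 4.5, 6.75 and 9.0 at the same four rates. Separation occurred in 6% of sets at a 10% rate and in 0.3% or fewer from 20% upwards. With 5 covariates the ratios are 1.5, 3.0, 4.5 and 6.0, and separation was 11%, 1%, 0% and 0%.

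**6. How easily the adjusted analysis is triggered.** The 16 clearly preoperative lines include surgeon (balanced by design) and one erectile-aid line. Leaving out surgeon and adding preoperative Gleason gives 16 baseline comparisons. If these were independent and tested at 5%, the chance of at least one significant difference would be 1 − 0.95^16 = 0.56. Correlated or discrete variables would change this, so it is only a rough guide. A difference judged clinically significant is a further route.

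**The case against.** The strongest reply is that the plan never says every Appendix A item enters the model. The phrase in IV.i does not name the appendix, which in fact comes after it, and IV.g describes data collection, not a model. IV.i opens with baseline characteristics and ties adjustment to differences arising from randomisation, so a sympathetic reader would expect imbalanced baseline variables only. The unadjusted tests come first. This stands in part. A reader might infer that the plan commits to a 33-term regression as its main analysis; the text does not support that. What remains is that the only list in view mixes baseline and post-assignment items, IV.g expressly counts surgery-specific variables as covariates, and no rule says which may be used. Section III was not in the text available; a covariate list there would change the reference.

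A second reply is that not every post-assignment item carries the effect. This also stands. Postoperative Gleason mainly reflects the tumour. Node template, assistant port and SV approach may be surgeon habit. The plan changes named in the surveys, nerve sparing and bladder neck preservation, are outcomes and not Appendix A covariates. None of this makes the technique and operative items baseline variables, and they have no role in correcting baseline imbalance.

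A third reply is that the fitting problem depends on event rates the documents do not give. That is correct. It is severe at 10 to 20%, modest at 30% and small at 40%.

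**Conclusion.** The concern holds in this form: the adjusted analysis has no defined covariate set, and the only list it can refer to is not restricted to pre-randomisation variables. Followed as written, it can bias the estimated effect of the 3D model. The direction depends on which variables are used. For a variable that carries part of a benefit, the estimate shrinks in proportion to that part (0.44 to 0.33, 0.22 or 0.11 SD under the assumed shares). Because adjustment is conditional, this affects the reported result only when the arms are judged to differ, but that trigger is broad.

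A reader might go further and conclude that the adjusted models cannot be fitted at all. The documents do not support that. Linear models for PSA and SHIM can be fitted with some loss of precision, and the logistic difficulty applies if the full list is entered and events are few. The event rates, mediated shares and independent simulated covariates are assumptions. The bias from conditioning on consequences of treatment does not depend on model size.

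**What to change.** In IV.i, replace the reference to covariates listed above with a short, named set of variables fixed before randomisation:

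- Surgeon, as the stratification factor, in every adjusted model (a random intercept fits the mixed models already planned).
- The relevant baseline value: for example preoperative PSA or risk category for oncologic outcomes, and preoperative SHIM for SHIM. Appendix A lists no baseline pad count, so the urinary models need their own choice, or surgeon alone.

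State that Appendix A sections 2 and 3, postoperative Gleason and postoperative erectile-aid use are not covariates in any treatment-effect model and are summarised by arm. Relabel the appendix to match. For extracapsular extension, perineural invasion, SV invasion and oncologic stage, record whether the value comes from preoperative imaging or biopsy, or from the specimen, and admit only the preoperative version. A penalised (Firth) logistic model can be named as the fallback when events are few.

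Which baseline items to choose is the trial team's decision; the essential step is to fix them before outcomes are compared by arm. The cost is one paragraph in IV.i and revised headings in Appendix A, with no new data and no change to the sample size.
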